#### Primary outcomes

2.13.1

NIHSS score and simplified fulg Meyer score were evaluated before and 10 days after treatment, and the data were analyzed by rank sum test or *χ*^2^ test. The modified Barthel index was evaluated before and 10 days after treatment and 30 days after treatment. The data were analyzed by rank sum test or *χ*^2^ test. The statistical significance between groups will show that there are differences in modified Barthel index, NIHSS score, and simplified fulg Meyer among groups after intervention.

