### Primary outcomes

2.9

NIHSS, score, and simplified fulg Meyer (FMA) score were evaluated before treatment and on day 10. The modified Barthel Index (MBI) was evaluated before and 10 days after treatment and 30 days after treatment

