### Estimation of sample size

2.11

This study is a preliminary clinical study to evaluate the efficacy and mechanism of targeted therapy before, after and during the follow-up period. We plan to enroll 42 participants in this study. (In this study, NIHSS score was used as the effect value. According to the sample size formula of good and bad clinical trials: N = 2δ^2^ × f(α,β)/(u_1_−u_2_)^2^. In the acupuncture group, the NIHSS mean value before treatment was 8.95, the standard deviation was 1.93, and the average NIHSS after treatment was 6.90, sou_1_ = 8.95, u_2_ = 6.90, δ = 1.93, α = 0.05, β = 0.1, f (α, β) = 10.5 from the table, which was substituted into the formula to calculate the sample size n ≈ 19 cases. Considering the loss rate of 10%, the total sample size required was 19 × 2 × (1 + 10%) ≈ 42 cases.)

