### Statistical analysis

2.13

According to the situation of data collection, data analysis will be based on the principle of intention to treat analysis (ITT) and/or per protocol analysis (PP). We will also evaluate the group effect by comparing the analysis results of the above 2 data sets to evaluate the accuracy of our analysis results.

All data will be analyzed by third-party statisticians using spss23.0 (v23.0, SPSS Inc, Chicago, IL). *P* < .05 was significant. Descriptive statistics will be carried out by group and time for average, standard deviation, maximum value, minimum value, and so on.

The data of the patients were collected and summarized. The quantitative indexes were *t* test and rank sum test. *χ*^2^ test (ANOVA) was used for non-rank counting, and rank sum test was used for grade counting. All statistical tests were performed with bilateral test. If *P* value is less than or equal to .05, the difference will be considered statistically significant.

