#### Secondary outcomes

2.13.2

The cortical excitability was evaluated on the day of admission and the 10th day of treatment respectively. The data obtained from the evaluation were analyzed by one-way ANOVA, and the classified result variables in the treatment log were compared by *χ*^2^ test.

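### Section 2.13.1 leaves the test for the primary scales open between rank sum and chi-square, conflicts with Section 2.13, and names no analysis that adjusts for baseline

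*Protocol article*

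**What the plan says.** Section 2.9 makes three scales primary. NIHSS and simplified Fugl-Meyer (FMA) "score were evaluated before treatment and on day 10", and the modified Barthel index (MBI) is taken before treatment and at two later times. A baseline value is therefore planned for every scale.

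Three places describe the tests:

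- **Section 2.13 (general rule):** "The quantitative indexes were *t* test and rank sum test". Chi-square is kept for unordered counts and rank sum for ordered ones. The abstract gives the same rule.
- **Section 2.13.1 (primary outcomes):** NIHSS and FMA "were evaluated before and 10 days after treatment, and the data were analyzed by rank sum test or" chi-square, and MBI is given the same pair. The aim is stated as "The statistical significance between groups will show that there are differences in modified Barthel index, NIHSS score, and simplified fulg Meyer among groups after intervention".
- **Section 2.13.2 (secondary outcomes):** for cortical excitability, measured at admission and on day 10, "The data obtained from the evaluation were analyzed by one-way ANOVA".

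No section says when rank sum or chi-square applies, where a score would be cut for chi-square, or whether post-treatment scores or changes from baseline are compared.

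**The concern.** The primary section offers two tests joined by an unexplained *or*, and one of them contradicts the general rule. This matters in three ways.

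1. **Loss of information.** Chi-square can be applied to NIHSS, FMA or MBI only after the score is cut into categories. That discards information, and the unstated cut point becomes a second open choice.
2. **Room to choose.** If the test is settled after the data are seen, the error rate for each scale can exceed the nominal 5%. The trial is open-label, so it helps to have the test fixed in advance.
3. **Unused precision.** Each patient's own starting score usually predicts the later score, yet no named method has it as a covariate. With about 19 evaluable patients per arm, that precision is worth having.

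**Working it through.** **Inputs from Section 2.11.** Difference 8.95 − 6.90 = 2.05 NIHSS points; SD 1.93; "α = 0.05, β = 0.1, f (α, β) = 10.5 from the table"; 19 evaluable per arm, 42 in total. Section 2.13 states "All statistical tests were performed with bilateral test", so all calculations are two-sided.

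**Assumptions not in the documents.** The baseline-outcome correlation r (shown for 0.3, 0.5 and 0.7), the chi-square cut point, normally distributed scores, and an illustrative difference of 1.5 points.

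**1. The plan's own figure.** n = 2 × 1.93² × 10.5 / 2.05² = 18.6, so 19 per arm; 19 × 2 × 1.1 = 41.8, so 42. The stated size reproduces.

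**2. Power of each named test at 2.05 points, 19 per arm.** The standard error of the difference is 1.93 × √(2/19) = 0.626. The t test has noncentrality 2.05 / 0.626 = 3.27 on 36 degrees of freedom, which gives 89%. Simulation (20,000 runs) gives:

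| Test | Power |
|---|---|
| t test | 88% to 89% |
| Rank sum | about 87% |
| Chi-square, assumed median split, no continuity correction | about 73% |

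Choosing between t test and rank sum costs about 2 points. Choosing chi-square costs about 15.

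**3. Error if the smaller p value is taken.** Simulated under no difference, per scale, at 19 to 21 per arm: the better of rank sum and uncorrected chi-square rejects in about 7% to 8% of trials. With the continuity correction the figure is about 5.5% to 6%, and close to 5% in some runs. These figures depend on the cut point and apply only if the choice is made that way.

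**4. Gain from baseline adjustment.** ANCOVA residual SD = 1.93 × √(1 − r²). Noncentrality = 1.5 / (residual SD × √(2/19)), with 36 degrees of freedom unadjusted and 35 adjusted.

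| r | 1 − r² | Residual SD | Noncentrality | Power for 1.5 points |
|---|---|---|---|---|
| unadjusted | 1 | 1.93 | 2.40 | 64% |
| 0.3 | 0.91 | 1.84 | 2.51 | 69% |
| 0.5 | 0.75 | 1.67 | 2.77 | 77% |
| 0.7 | 0.51 | 1.38 | 3.35 | 90% |

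A normal approximation gives figures 2 to 3 points higher (67%, 71%, 79%, 92%) and the same pattern. At the full 2.05 points, power is already 89% unadjusted, so the gain matters mainly for smaller effects. A smaller effect is plausible here, because 2.05 is a before-after change within an acupuncture group and not a difference between arms.

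**5. Change scores as an alternative.** The SD of change is 1.93 × √(2(1 − r)). At r = 0.5 this is 1.93 again, so nothing is gained over comparing post-treatment scores. At r = 0.3 it is 2.28, which is worse. ANCOVA is at least as precise at every r shown.

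**6. Chance imbalance at baseline.** With 21 per arm the standard error of the baseline difference is 1.93 × √(2/21) = 0.596. The probability of a difference above 1 point is P(|Z| > 1 / 0.596 = 1.68) = 0.093, about 9%.

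**The case against.** The strongest reply is that this is a condensed article by a self-described pilot study, and the analysis plan is not shown. Whether post-treatment scores, changes or a covariate are used is commonly left to that plan. The scales can also be read as ordered data, in which case rank sum satisfies both Section 2.13 and Section 2.13.1, and the t test is never assigned to them in 2.13.1. Third-party statisticians do the analysis, which makes deliberate selection less plausible.

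Much of this stands, and it rules out four stronger readings that a reader might infer:

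- **That the plan ignores baseline.** The text is silent. A rank sum test or ANOVA on change scores is neither stated nor excluded.
- **That unadjusted tests are invalid.** In a randomised comparison they are valid, and their error rate already allows for chance imbalance. The same holds for one-way ANOVA on cortical excitability.
- **That a material baseline imbalance is likely.** About 9% for more than 1 NIHSS point is not likely.
- **That the error rate is in fact inflated.** That needs an assumed cut point and selection of the smaller p value. The continuity correction removes most of the excess, though it lowers chi-square power further.

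The reply does not dispose of the unexplained *or*, or of chi-square being attached to scale scores against the general rule. Those are statements the article makes, not details it leaves out, and an unseen plan cannot make them agree.

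**Conclusion.** The point holds in a limited form. Section 2.13.1 fixes the primary test badly: it gives two options with no rule, and one of them is inconsistent with Section 2.13 and the abstract and unusable without an unstated cut point. Using that option would cost about 15 points of power at the plan's own effect, assuming a median split. The possible error inflation is modest and conditional.

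Baseline adjustment is an improvement in precision, not the repair of an invalid test. Its value depends on a correlation the documents do not give: for a 1.5-point difference, about 4 to 5 points of power at r = 0.3 and about 26 at r = 0.7. The change should be made before analysis, but the trial's validity does not hang on it.

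**What to change.** 1. In Section 2.13.1, name one primary analysis per scale and time point: NIHSS and FMA at day 10, and MBI at each of its two post-baseline assessments, each by ANCOVA with treatment arm and the baseline value of the same scale. Report the adjusted mean difference with its 95% confidence interval.
2. Name one sensitivity analysis, rank-based ANCOVA, with no alternative beside it.
3. Remove chi-square for these scores, and make the abstract, Section 2.13 and Section 2.13.1 agree. Section 2.13 also puts ANOVA in brackets after chi-square, which should be corrected in the same edit.
4. As a free improvement, use the same baseline-adjusted model for day-10 cortical excitability in Section 2.13.2.

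This changes analysis wording only. The baseline data are already planned, ANCOVA is available in the planned SPSS software, and no patients or visits are added. It does not address multiplicity across the several primary comparisons, which is a separate matter.

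### Three primary scales give four between-group tests, each at two-sided .05, with no single primary endpoint and no stated success rule, although the trial is sized on NIHSS alone

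*Protocol article*

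**What the plan says.** Protocol article, section 2.9 (Primary outcomes), puts three scales under one heading without ranking them. For the first two, "NIHSS, score, and simplified fulg Meyer (FMA) score were evaluated before treatment and on day 10". The third, the MBI, "was evaluated before and 10 days after treatment and 30 days after treatment". That makes four post-baseline comparisons between the groups: NIHSS day 10, FMA day 10, MBI day 10 and MBI day 30.

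Section 2.13 (Statistical analysis) sets one threshold for everything. "All statistical tests were performed with bilateral test", and if the P "value is less than or equal to .05, the difference will be considered statistically significant".

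Section 2.13.1 repeats the three scales and describes how a result will be read: "The statistical significance between groups will show that there are differences in modified Barthel index, NIHSS score, and simplified fulg Meyer".

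Section 2.11 (Estimation of sample size) uses one scale only: "In this study, NIHSS score was used as the effect value". It does not call NIHSS the sole or main primary outcome.

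**The concern.** The trial has several primary comparisons and one uncorrected threshold, and no rule connects the four P values to one conclusion. A reader cannot tell whether the efficacy claim needs NIHSS, all three scales, or any one of them. Nor is it clear which MBI time point counts.

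If the claim may rest on whichever comparison reaches .05, its error rate exceeds the 5% that applies to each test. If all must succeed, the error rate is controlled, but a sample size set for NIHSS alone does not secure the stated 90% power for the joint claim. Either way, the primary conclusion is not tied to the endpoint on which the trial was planned.

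The trial is open-label with 21 patients per group, so freedom to choose among results afterwards matters. The plan also leaves open rank sum or chi-square for the primary scales, and intention-to-treat and/or per-protocol for the analysis set. The figures below do not count that further freedom.

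**Working it through.** **1. The plan's own figure.** Section 2.11 gives means 8.95 and 6.90 (difference 2.05), SD 1.93, α = 0.05, β = 0.1 and f(α, β) = 10.5.

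- Per group: 2 × 1.93² × 10.5 / 2.05² = 78.22 / 4.2025 = 18.6, so 19.
- Total with 10% loss, computed as the plan does: 19 × 2 × 1.10 = 41.8, so 42.

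The stated 42 is reproduced. It is a calculation for one test of one scale at .05.

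**2. Number of primary tests.** NIHSS (1) + FMA (1) + MBI (2) = 4, or 3 if only one MBI time point counts.

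**3. Chance of at least one false positive, independent tests.** The formula is 1 − 0.95^k.

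- k = 4: 1 − 0.8145 = 18.5%.
- k = 3: 1 − 0.8574 = 14.3%.

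**4. The same with correlated tests.** The scales are measured in the same patients and will correlate. The documents give no correlations, so the values below are assumptions. Normal test statistics with a common correlation were simulated (2 million draws, two-sided .05 each).

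| Assumed correlation | Four tests | Three tests |
|---|---|---|
| 0 | 18.5% | 14.3% |
| 0.3 | 17.4% | 13.7% |
| 0.5 | 15.6% | 12.5% |
| 0.7 | 13.0% | 10.9% |
| 0.8 | 11.4% | 9.8% |
| 0.9 | 9.4% | 8.4% |

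Two of the four tests use the same scale at two times, so a mixed structure is more plausible than independence. With the two MBI tests correlated at 0.85 and all other pairs at 0.3, 0.5 or 0.7, the results are 15.7%, 14.5% and 12.6% (1 million draws each).

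**5. The opposite rule.** If all four had to be significant, the error rate could not exceed 5%. In the simulation it was 1.0% at correlation 0.8 and 1.9% at 0.9.

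**6. What different repairs cost.** These figures use the plan's own inputs.

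- One primary endpoint at .05: error rate 5%. With NIHSS, 19 per group and a total of 42 stand, and power with 19 evaluable per group is 90.6%.
- Bonferroni over four tests (.05 / 4 = .0125): 26 per group, 26 × 2 × 1.10 = 57.2, so 58 in total. Alternatively, power with 19 per group falls to 78%.
- Bonferroni over three tests (.05 / 3 = .0167): 24 per group, or 81% power with 19 per group.

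The sample sizes and powers are illustrative only. The 2.05 in section 2.11 is a before-to-after change in an acupuncture group, not a difference between two treatments.

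**The case against.** **A reader might infer that the plan counts any one significant scale as success, and that its error rate is therefore 11% to 18%.** The documents do not support that as a statement of the plan. The sentence in section 2.13.1 joins the three scales with an and, and it defines neither an any-one nor an all-must-succeed rule. It can also be read as three separate claims, each about its own scale and each with a 5% error rate. The inflation belongs to the any-one reading alone. This objection stands, and it makes the percentages conditional.

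**No overall 5% is promised.** This is true: section 2.13 sets a per-test threshold, and the α in section 2.11 belongs to the NIHSS calculation. The gap remains, because the article still draws one efficacy conclusion from these tests without saying how.

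**Independence is unrealistic.** This stands as well. The 18.5% is an upper reference value, and 12.6% to 15.7% is more plausible under the mixed structure, still on assumed correlations.

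**It is a pilot.** Section 2.11 calls the study preliminary and the Discussion calls it a pilot. But the Discussion and the Abstract's conclusion also speak of proving efficacy, and the sizing is a formal 90% power calculation. The pilot label does not cover claims of that kind.

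**This belongs in the analysis plan.** Adjustment methods and test order commonly do, and their absence from an article is not the point. The point is what the article itself fixes: several unranked primaries, one threshold for each, and a sample size for only one of them.

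**Conclusion.** The point holds in conditional form. Sections 2.9 and 2.13.1 make three scales and four between-group comparisons primary, each at two-sided .05, with no single primary, main MBI time point or success rule, while section 2.11 rests on NIHSS alone.

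If one significant result is allowed to carry the efficacy claim, the false-positive risk is above 5% at every correlation examined. For four tests it runs from 18.5% (independent) to about 9% (common correlation 0.9). This rests on the any-one reading, which the text leaves open but does not state, and on assumed correlations. The text should be settled before data are seen, because afterwards any choice of rule could be guided by the results.

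**What to change.** In sections 2.9 and 2.13.1, name one primary endpoint and one time point before data are seen, and state that the efficacy conclusion rests on that test at two-sided .05.

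- NIHSS at day 10 is the choice consistent with section 2.11 and leaves the total at 42.
- The trial's stated aim is limb function, so the investigators may prefer FMA. In that case section 2.11 must be restated with FMA inputs. The choice is theirs to justify.

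Make the remaining scales and time points secondary and report them as between-group estimates with confidence intervals. If formal claims on them are wanted, test them only after the primary is significant, either in an order written down in advance or with Holm's procedure across them.

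The cost is wording, with no added patients if NIHSS is kept. The real downside is that a lone positive result on a non-primary scale can no longer carry the primary claim.

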#### Secondary outcomes

2.13.2

The cortical excitability was evaluated on the day of admission and the 10th day of treatment respectively. The data obtained from the evaluation were analyzed by one-way ANOVA, and the classified result variables in the treatment log were compared by *χ*^2^ test.

#### Safety evaluation

2.13.3

Adverse events recorded in the patient log will be analyzed as multiple variables. The number and percentage of AE patients were calculated and compared by *χ*^2^ test.

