**Conclusion::**

The purpose of this study was to determine the effect of repetitive magnetic stimulation of M1 region combined with magnetic stimulation of Neiguan and Sanyinjiao points on limb function after stroke. Through this study, we expect to explore a new scheme for the treatment of poststroke dyskinesia, and prove that compared with rTMS and acupuncture alone, the closed-loop rehabilitation theory based on “center peripheral center” can be more efficient and safe in the treatment of poststroke limb dysfunction.

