### Study group

2.5

In this study, 42 patients who met the inclusion criteria and obtained informed consent were selected as the research subjects. The subjects were randomly divided into 2 groups according to the ratio of 1:1: the experimental group and the control group, with 21 cases in each group.

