#### Positive-control group

2.7.2

In addition to the basic treatment, the patients in the control group also need to be given corresponding acupuncture treatment. According to the theory of traditional Chinese medicine, acupuncture position and parameters were selected^[19,20]^: upper limbs (bilateral): Hegu, Neiguan, Shousanli, Quchi, Jianli; lower limbs (bilateral): Taichong, Xuanzhong, Sanyinjiao, Zusanli, Yanglingquan, Fengshi; head: Baihui, Fengchi (bilateral). Patients will be treated once a day for 10 consecutive days.

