#### Adverse reactions and countermeasures of magnetic stimulation

2.8.1

Magnetic stimulation may induce epilepsy, local skin numbness, pain and discomfort, and other adverse reactions. In the treatment process, the intensity, frequency, and stimulation times can be changed according to the patient's condition to reduce the occurrence of adverse reactions.^[21–23]^ During the study, a patient treatment log will be established to monitor all adverse reactions during treatment and follow-up, and appropriate intervention will be carried out. If serious adverse reactions occur during the treatment, they should be reported to the principal investigator immediately, and the details should be recorded in the patient's treatment log and corresponding treatment measures should be taken, such as adjusting the coil position and stimulation intensity to avoid stimulating the sensitive orbitofrontal cortex (100% RMT → 80% RMT), or giving appropriate medical intervention according to the patient's condition. If the subject or researcher thinks that the patient cannot tolerate these adverse reactions, the trial can be terminated and the subject will withdraw from the study.

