#### Adverse reactions of acupuncture and countermeasures

2.8.2

Acupuncture may cause acupuncture syncope, convulsion, severe pain, stuck needle, broken needle, local infection and subcutaneous hematoma and other adverse reactions. However, they are generally mild reactions, and the prognosis is generally good after corresponding treatment.^[24]^ According to the causes of adverse reactions and the degree of adverse reactions, symptomatic treatment can be carried out, such as: detailed medical history to avoid convulsion, appropriate psychological counseling to avoid fainting, standardized needle application, auxiliary manipulation to avoid needle sticking, pain, broken needle, etc. If there are serious adverse reactions, they should be reported to the principal investigator immediately, and the details of adverse reactions should be recorded in the patient's log, and medical intervention should be carried out. If the subject or researcher thinks that the patient cannot tolerate these adverse reactions, the trial can be terminated and the subject will withdraw from the study.

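### The one safety comparison specified, a chi-square test on the percentage of AE patients with 21 per arm, ignores type and seriousness and cannot support the expected conclusion on safety

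*Protocol article*

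**What the plan says.** Section 2.13.3 of the protocol article (Safety evaluation) has two sentences. The first is "Adverse events recorded in the patient log will be analyzed as multiple variables"; it does not say which variables. The second is "The number and percentage of AE patients were calculated and compared by *χ*^2^ test". No other between-arm analysis of adverse events is specified, and neither sentence mentions type, seriousness or severity.

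The abstract's conclusion expects to prove that the closed-loop treatment, compared with rTMS and acupuncture alone, "can be more efficient and safe in the treatment of poststroke limb dysfunction".

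The risks are set out separately for each arm. Section 2.8.1 says "Magnetic stimulation may induce epilepsy, local skin numbness, pain and discomfort, and other adverse reactions". Section 2.8.2 lists fainting, convulsion, severe pain, stuck or broken needle, infection and haematoma for acupuncture, and adds "However, they are generally mild reactions, and the prognosis is generally good after corresponding treatment". Section 2.5 fixes the arms: "the experimental group and the control group, with 21 cases in each group".

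**The concern.** A percentage of AE patients answers a safety question only if the events counted are broadly comparable between arms. Here they need not be. The control arm is needled at many points every day, so its patients have many chances of a small local reaction. The experimental arm has magnetic stimulation, for which epilepsy is the first risk named. In the planned count, a patient with a small haematoma and a patient with a seizure each contribute one.

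The stake is the reading of the result. A surplus of mild events in the control arm could give p < .05 and be reported as supporting the safety claim in the abstract, while saying nothing about the rare serious event. Conversely, a non-significant result at this size would be no evidence that the serious risks are equal.

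**Working it through.** **1. Sample size.** Section 2.11 sets the number of patients on NIHSS, not on safety, with "α = 0.05, β = 0.1, f (α, β) = 10.5 from the table", a difference of 8.95 − 6.90 = 2.05 and SD 1.93. Then 2 × 1.93² × 10.5 / 2.05² = 18.6, so 19 per arm, and 19 × 2 × 1.1 = 41.8, so 42. The stated figure reproduces. It was never meant to give precision on adverse events.

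**2. Exposure in the control arm.** Section 2.7.2 lists five bilateral upper-limb points, then "lower limbs (bilateral): Taichong, Xuanzhong, Sanyinjiao, Zusanli, Yanglingquan, Fengshi; head: Baihui, Fengchi (bilateral"). Counting them gives 5 × 2 + 6 × 2 + 1 + 2 = 25 points per session. Over 10 days that is 250 insertions per patient, assuming one needle per point. For illustration only: if a minor event followed an insertion with independent probability r, the share of control patients with at least one would be 1 − (1 − r)^250. This is 11.8% at r = 0.05%, 22.1% at 0.1% and 71.4% at 0.5%. The document gives no such rate, and no matching rate for magnetic stimulation. The range shows how exposure drives the count; it does not predict a difference between arms.

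**3. What 21 patients can say about seizure.** With zero events in n = 21, the exact one-sided 95% upper bound is 1 − 0.05^(1/21) = 13.3%. The upper limit of a two-sided 95% interval is 1 − 0.025^(1/21) = 16.1%. The chance of seeing at least one seizure is 1 − (1 − p)^21. At assumed true risks of 1%, 2% and 5% it is 19.0%, 34.6% and 65.9%. Two seizures against none gives chi-square p = 0.147 (Fisher's exact test 0.49).

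**4. What the planned test can declare.** For 1 of 21 against 6 of 21, uncorrected chi-square = 42 × (1 × 15 − 6 × 20)² / (21 × 21 × 7 × 35) = 4.29, so p = 0.038. The arm with one AE patient is favoured whatever that event was. Three splits in which the experimental arm has fewer AE patients:

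| Experimental v control (of 21 each) | Chi-square, uncorrected | Continuity-corrected | Fisher | Expected AE patients per arm |
|---|---|---|---|---|
| 0 v 4 | 0.035 | 0.115 | 0.107 | 2 |
| 1 v 6 | 0.038 | 0.098 | 0.093 | 3.5 |
| 2 v 8 | 0.030 | 0.070 | 0.067 | 5 |

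**5. Is the chi-square test itself at fault?** Enumerating all 21 v 21 tables at a 5% significance level, the uncorrected test has a true type I error of 0.1% at a common AE rate of 2%, 1.3% at 5%, 4.1% at 10% and 5.2% at 20%. Its maximum is 5.6%, near a rate of 30%. Fisher's test stays at about 2.3% or below. The error rate is therefore close to nominal or under it. The problem is what is counted and what is concluded from it.

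**The case against.** **The text does not fix a single pooled test.** Section 2.13.3 first says that several AE variables will be analysed, and section 2.13.2 compares categorical variables from the treatment log. This stands in part: a reader might infer that one test on any AE is all that is planned, and the document does not say so. But the several variables are undefined, and the percentage of AE patients is the only summary given with a test.

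**Acupuncture risks are not merely trivial.** A reader might infer a clean contrast between mild needling events and seizure. Section 2.8.2 also names convulsion, severe pain and broken needle, and section 2.8.1 names numbness and discomfort for magnetic stimulation. This stands: an excess of mild events in the control arm is possible but not shown. It also supports reporting by type, because a convulsion in either arm would be lost in the total.

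**The chi-square p-value is not too small.** A reader might infer that it is from the gap to Fisher's test. The enumeration does not support that: the gap mostly reflects Fisher's conservatism, and the document does not say whether a continuity correction would be used. An exact test is only a cautious option for sparse tables.

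**No decision rule ties this test to a safety claim.** The abstract states an expectation, and the Discussion calls the study a pilot with a small sample. This stands as mitigation, but the Discussion does not withdraw the safety expectation.

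**Seizures would not go unnoticed.** Serious reactions go at once to the principal investigator and are logged, and the ethics committee reviews serious adverse events. That is true of oversight during the trial; it does not alter what the specified comparison can show. An analysis plan that is not shown may also carry severity tables. The point therefore rests on the method the article does state and on the conclusion it expects.

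**Conclusion.** The point holds in a limited form. The one safety comparison that section 2.13.3 specifies does not separate events by type or seriousness. With 21 per arm it cannot deliver the safety half of the conclusion the abstract expects. Zero seizures would be compatible with a true risk of up to 13.3% (one-sided) or 16.1% (two-sided limit), assuming all 21 patients are observed. A nominally significant result in favour of magnetic stimulation can arise at 1 against 6 AE patients, even when the single event is the serious one; the p = 0.038 assumes no continuity correction. The per-insertion range is illustrative and carries no weight in this conclusion. The planned efficacy analysis is not affected.

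**What to change.** In section 2.13.3, state which AE variables are meant. Report the number and percentage of AE patients per arm by type and by seriousness or severity, with seizure or convulsion shown as its own line in both arms, and with exact confidence intervals. Describe any between-arm test as descriptive, and use an exact test where expected counts fall below 5.

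In the abstract's conclusion, replace the safety part with a statement that the trial describes the tolerability of the two treatments and cannot establish that the combination is safer.

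The change adds no patients, visits or procedures, since adverse reactions are already to be recorded in the log and case report form; at most the record needs a field for type and seriousness if it lacks one. The cost is a less favourable safety claim.
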